**Figure 3 F3:**
[figure not shown]
Potential Structural Equation Model.

Therefore the following will be tested:

i. the (lag 1) effect of fluoride intervention on the subsequent oral health assessment (parameters a_1_, a_2_ a_3_);

ii. a test of stability or equivalence of effect by constraining the parameters a_1_, a_2_ a_3_ (solid lines) to be equal and examining the significance of loss of ‘close fit
[42]’.

iii. a test of the longer term effect (lag 2) of fluoride intervention beyond immediate subsequent oral health assessment controlling for lag 1 effects, as shown by parameters b_1_ and b_2_(dotted line).If these parameters are shown to be significant in this more complex model then an additional enquiry can be performed to test for the equivalence of these two lag 2 coefficients.

Although the health education intervention builds over 2 years the essentials of the appropriate health behaviours are built into the first 3 visits (shaded rectangle in Figure
3), controlling the night time bottle, reducing sugar consumption between meals, using a toothbrush, and applying fluoride toothpaste twice a day. Effectiveness is measured in terms of the caries screening and the final (30 month) full dental examination.

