### Statistical analysis

The primary analysis will be an evaluation of the estimated prevalence of caries at 30 months in relation to the null hypothesis that the rate is 2. Descriptive analyses of other endpoints will be applied using methods appropriate for continuous and categorical data. Estimates will be presented with two-sided 95 percent confidence intervals.

The qualitative data from the interviews will be analyzed , using the ‘framework’ method
[38]. The qualitative data will be fractured and examined for key topic areas. The data will then be systematically coded according to the topic areas and thematic charts (in spreadsheet form) will be constructed. Summaries of the relevant parts of transcripts will be written into the charts so that each case may be examined across a range of different and emerging themes
[38].

The proposed study is rare in health promotion research in that it is not a ‘before and after’ design but is longitudinal, building information and capacity over time
[39]. The longitudinal design helps the investigative team to test for mediation effects in a more rigorous manner than cross sectional designs
[40]. For example the multi-wave nature of the assessments delivers the following methodological advances:

i. prevention on the reliance of retrospective reports of health behavior from mothers (removal of memory biases);

ii. reliable baseline latent variables of fluoride use and oral health (reducing bias of measurement error);

iii. enable the testing of growth models and unbiased parameter estimation of the fluoride intervention using resampling methods (bootstrapping). This third improvement would be made possible by controlling for concurrent baseline disease levels. Cole and Maxwell
[39] suggest that Structural Equation Modelling (SEM) will greatly assist in testing the direct and indirect effects of a longitudinal intervention. Crucial is the development of a model which can reduce bias frequently inherent in two wave designs. These are sometimes referred to as ‘half-longitudinal’
[41]. The proposed design therefore has innovative features not utilized in previous caries prevention programs which will enable true longitudinal investigation benefiting from the latest developments in statistical modeling.

One potential model which could be assessed utilizing Structural Equation Modeling is shown in Figure

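### The structural equation model's coefficients are named as unbiased effects of fluoride, but the visits deliver a four-part package, so the stated text does not support a fluoride-specific reading

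*Protocol article*

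**What the plan says.** Three parts of the Statistical analysis section of the protocol article bear on this point.

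- **The tests.** Those listed after Figure 3 are presented as work that will be done. Test (i) concerns the lag 1 "effect of fluoride intervention on the subsequent oral health assessment", with parameters a1 to a3. Test (ii) constrains the same three parameters to be equal. Test (iii) is "a test of the longer term effect (lag 2) of fluoride intervention beyond immediate subsequent oral health assessment controlling for lag 1 effects", with parameters b1 and b2.
- **The claimed advantages.** The design is said to provide "reliable baseline latent variables of fluoride use and oral health", and to allow growth models and "unbiased parameter estimation of the fluoride intervention using resampling methods (bootstrapping"). The support offered is one sentence: "This third improvement would be made possible by controlling for concurrent baseline disease levels".
- **The content of the visits.** The paragraph after the tests says that the essentials are built into the first three visits, shown as a shaded rectangle in Figure 3. It lists them as "controlling the night time bottle, reducing sugar consumption between meals, using a toothbrush, and applying fluoride toothpaste twice a day".

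Other sections describe the same package. The program strategies at the start of Methods/Design include bottle control, brushing, fluoride toothpaste and less frequent sugar. The Data collection section records bottle use, brushing, toothpaste use and diet. The Abstract describes a single-arm trial of a dental health education program. The Discussion says the model's pre-determined effects are for testing the efficacy of the program.

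**The concern.** The article gives two accounts of what a1 to a3 and b1 to b2 represent. The list of tests says fluoride; the Discussion says the program. Because one health worker gives all the advice in the same visits to every family, no group receives the other components without fluoride toothpaste. Any separation of fluoride from the rest must come from differences between families in what they take up. Families who take up the toothpaste advice may well take up the bottle and sugar advice too.

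This is a question of which part of the package a coefficient stands for. It is separate from the absence of an untreated group. At stake is the interpretation of the secondary modelling: a coefficient reported as the immediate or longer-term effect of fluoride could contain the effects of the other behaviours, under a claim of unbiasedness that the stated adjustment does not support.

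**Working it through.** The article gives no figure for this point, so there is none to reproduce. The check has two parts.

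**1. The two readings of the exposure.**

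| Reading of the exposure | What the coefficient is | Does the stated property hold? |
|---|---|---|
| Receipt of the visits | Effect of the whole package | No. The name is wrong, and the components cannot be separated because every child is offered the same visits. |
| Reported fluoride use | Association of fluoride use with later oral health | Not from the stated support. Baseline disease is the only adjustment named, and it does not remove correlation between fluoride use and the other behaviours. |

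Bootstrapping supplies standard errors and intervals. It does not remove bias from an omitted variable.

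**2. How large the second problem could be.** The article gives neither uptake correlations nor component effects, so all inputs here are assumptions. Take standardised uptake scores, a common pairwise correlation r, and a model that contains fluoride use alone. Then

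fluoride coefficient = b_F + r × (sum of the omitted effects).

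With k omitted behaviours, each with the same true effect as fluoride (set to 1), this is 1 + k × r:

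| r | k = 1 | k = 2 | k = 3 |
|---|---|---|---|
| 0 | 1.0 | 1.0 | 1.0 |
| 0.3 | 1.3 | 1.6 | 1.9 |
| 0.5 | 1.5 | 2.0 | 2.5 |
| 0.8 | 1.8 | 2.6 | 3.4 |

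On a standardised scale, one omitted behaviour, r = 0.5 and true paths of 0.15 give 0.15 + 0.5 × 0.15 = 0.225. With a true fluoride path of zero, the result is 0 + 0.5 × 0.15 = 0.075.

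The Study design section plans 150 children and allows for 33% attrition, which leaves 150 × (1 − 0.33) = 100.5, about 100. A simulation of 4,000 trials of 100 children per setting assumed no fluoride effect and three omitted behaviours with effects of −0.2 each (residual SD 1). The expected fluoride coefficient is r × 3 × (−0.2).

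| r | Expected | Simulated mean | Fluoride path significant at 5% |
|---|---|---|---|
| 0 | 0 | 0.001 | 5% |
| 0.3 | −0.18 | −0.180 | 38% |
| 0.5 | −0.30 | −0.301 | 79% |
| 0.8 | −0.48 | −0.480 | 99% |

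These are single-equation illustrations. They contain neither the baseline-disease term nor the lagged structure of the planned model. They show the direction of the problem and its dependence on r. They are not an estimate of the bias in this trial.

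**The case against.** The strongest case on the other side has four parts.

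- **The model is drawn in Figure 3, which is not available here.** The text ties the four behaviours to a shaded rectangle in that figure, so paths for bottle, sugar or brushing may be there. This stands. A reader might infer that the model has a fluoride-only path and that the package's effect will be credited to fluoride. The documents do not establish that.
- **The model is provisional.** It is introduced as one potential model, and an article commonly leaves its full specification to the analysis plan. This limits the weight of the point. It does not remove it, because the tests are stated as planned and the unbiasedness claim is made outright; both name fluoride alone.
- **The term may be shorthand for the program.** The paragraph after the tests speaks of the health education intervention, and no passage states an aim of isolating fluoride. This is plausible. On that reading the defect is one of naming, which is what the main fix corrects.
- **Phase III does not depend on these coefficients.** A reader might infer that Phase III could be built around fluoride when another component did the work. The documents do not support this: the Study design section rests the case for Phase III on rejecting the primary null hypothesis, and the primary analysis attributes nothing to fluoride.

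It is also fair to say that a single figure, such as a coefficient 50% too large, would rest wholly on assumed inputs.

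**Conclusion.** The point holds as one of labelling and interpretation in the secondary modelling. As the text stands, a1 to a3 and b1 to b2 cannot be read as unbiased effects of fluoride. If the exposure is the visits, the name is wrong. If it is reported fluoride use, the named adjustment for baseline disease leaves it open to confounding by the other behaviours, unless Figure 3 or the full plan models them.

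No size can be fixed from the document. There is no bias from this source if uptake of the behaviours is uncorrelated or if the omitted behaviours have no effect. Otherwise, with effects in the same direction and positive correlation, the fluoride coefficient is inflated, and more so as the correlation rises. The primary analysis of caries at 30 months and the sample size are not affected.

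**What to change.** In the Statistical analysis section, rename the exposure, and with it a1 to a3 and b1 to b2, as effects of the program or of a latent variable for the program behaviours. This agrees with the Discussion. Delete the claim of unbiased estimation for a fluoride effect, and word the conclusions of tests (i) to (iii) in the same terms. If Figure 3 already contains the other behaviours, say so in the text.

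Component-specific paths could be added as an exploratory sensitivity analysis only, using the bottle, diet and brushing data that the questionnaire already collects. With about 100 completers and correlated behaviours, the intervals would be wide and the components might not be separable.

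The main change costs wording only. It needs no new data and does not alter the sample size.

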## Methods/Design

The aim of the program of research is to address the need to improve the oral health of Aboriginal children
[10-12]. The objective of the study is to build upon the success of the pilot work, using a phase II single arm trial design to gather preliminary evidence on the effectiveness of the program offered to Aboriginal children from six months of age who are at risk of dental caries. The program will be assessed over a period of 2 years to investigate not only the effectiveness, but also its feasibility and to inform the design of a subsequent confirmatory randomised phase III trial. The research follows the MRC framework for the design and evaluation of complex interventions to improve health
[13]. The primary endpoint is the prevalence of early childhood caries at 30 months of age. Secondary endpoints include: changes in primary caregivers dental knowledge over time; number of episodes of dental care; impact of oral health problems on the family and qualitative measures of the program to assess its acceptability to the families. In addition the managers and Aboriginal Health Workers will be interviewed to record their views on the overall feasibility and sustainability of the program
[14].

The pilot work and consultation with ACCHSs led to the development of the dental health education program which is characterized by the following strategies:

Delivery by trained Aboriginal Health workers;

Support for health oral behaviours offered to families with young children;

Focus on control of the night time bottle, toothbrushing and use of fluoride toothpaste;

Free toothpaste, and toothbrushes for all the family together with a ‘sippy’ (trainer) cup for the child;

Restricting the frequency of the consumption of sugary snacks and drinks.

Careful attention to the cultural appropriateness of teaching materials.

The development of the ACCHSs capacity to provide oral health support to vulnerable families through the development of the role of AHWs is based on Goodman’s model of organizational change
[15].

The development of the oral health role of Aboriginal Health Workers is strongly supported by the National Aboriginal Community Controlled Health Organisation
[16], the Australian Dental Association
[17], Australia‘s National Oral Health Plan
[18], and the National Aboriginal and Torres Strait Islander Oral Health Workshop

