[19]. Despite the extent of this support and the National Aboriginal Community Controlled Health Organization calling for the development of this role for over a decade there has been little sustainable development of the role of AHWs, and there has been no evaluation of the impact of such a role on the oral health of Aboriginal families. The disconnect between policy and practice in this area and the identification of facilitators and barriers to the development of this role has been the subject of recent research
[20].

The program focuses on family/carers because they significantly influence whether a child will develop Early Childhood Caries (ECC) and will be responsible for establishing long lasting family norms of behaviour regarding tooth brushing behaviour and diet
[21,22]. In order to support family/carers, AHWs will, systematically at predetermined intervals, provide them with oral health products, education materials, advice specific to the dental needs of the child and screen for early signs of ECC. This is an innovative approach to the prevention of oral disease in Aboriginal communities which contrasts the current model, whereby health education is delivered at irregular intervals.

The development of family knowledge and norms about the value and care of the primary dentition is important because many parents have the ‘commonsensical belief’ that if teeth do not hurt there are no dental problems
[23,24]. Given this belief and the rapid progression of the disease, dental care may not be sought until the child requires hospitalization for dental extractions under general anaesthesia. Hence, the inclusion of oral health screening is an integral part of the program.

The value of strategies which focus on families with young children is further emphasised by research which has shown that a child with one carious lesion is five times more likely to develop a further carious lesion than a child with no dental caries
[25]. This difference in risk is of major significance and demonstrates that early intervention to maintain a child’s oral health is the most logical and practical preventive strategy.

A lack of family carer access to dental health education and oral care products is a major barrier to maintaining a healthy mouth. Kruger et al
[26] reports a significant lack of oral health awareness among Aboriginal people. The National Rural Health Alliance reports that 30 percent of Indigenous children do not own a toothbrush

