### Dental health education program

The visit program is outlined in Figure
1 and centres on avoiding using a ‘bottle’ as a night –time comforter, using fluoride toothpaste from 9 months of age, encouraging the whole family to brush and having a simple oral health screening by the AHWs to assess whether early signs of dental caries are evident. Culturally appropriate leaflets and fridge magnets will be offered and an advice line is available should any of the families have specific problems. An example of one of the leaflets is shown in Figure
2.

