### Data collection

Information on baseline and subsequent visits (Figure
1) will be collected by the AHWs utilizing a structured questionnaire which has been piloted in an Aboriginal community.

The key topics for intervention are:

Bottle use, when and what to put in it.

Tooth brushing – using the tooth brush

Toothpaste - using the toothpaste, how much to put on the brush and safe storage

Dietary habits – reported changes in the consumption of sugary snacks and drinks

AHWs screen for caries
[35] – positive/negative

Reported dental problems

At the final 30-month assessment the carers will be asked about their perceptions of the feasibility, and acceptability of the program. In addition selected questions from the Dental Discomfort Scale
[36] and the Being a Mother Scale
[37] will be included in the assessment. The Aboriginal Health Workers and the senior management team at each AMS will be interviewed to record their views on the facilitators and barriers to the wider implementation of the program. All interviews will be recorded, transcribed and analyzed for recurrent themes.

The end of trial dental assessment will be undertaken by a calibrated examiner using the same diagnostic criteria when collecting the dental caries data on the historical reference group.

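### The health workers' caries screen is named as a measure of effectiveness, but neither the screen nor the model paths that rely on it can by themselves show that the program works

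*Protocol article*

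**What the plan says.** The structural equation modelling text that ends the Statistical analysis section closes with this statement: "Effectiveness is measured in terms of the caries screening and the final (30 month) full dental examination". It sets two measures side by side and does not rank them.

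The protocol describes the screen in three places.
- Dental health education program describes it as "having a simple oral health screening by the AHWs to assess whether early signs of dental caries are evident".
- Data collection lists it among the visit topics with the entry "35] – positive/negative" (the number is a citation).
- Methods/Design treats it as part of the intervention: "Hence, the inclusion of oral health screening is an integral part of the program".

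The same workers deliver the program. Methods/Design lists "Delivery by trained Aboriginal Health workers" as a program strategy and says AHWs will "provide them with oral health products, education materials, advice specific to the dental needs of the child and screen for early signs of ECC". Information from the baseline and later visits, including brushing and toothpaste use, "will be collected by the AHWs utilizing a structured questionnaire which has been piloted in an Aboriginal community".

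The final examination is different: "The end of trial dental assessment will be undertaken by a calibrated examiner using the same diagnostic criteria", namely those used for the historical reference group. The primary endpoint (Methods/Design) is caries at 30 months. The primary analysis (Statistical analysis) tests that result against a null value of 2, and Study design makes rejection of that null the case for Phase III.

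**The concern.** A measure of program effect needs two things: some indication of what it would have read without the program, and readers whose judgement does not depend on the program. The 30-month examination has a reference group and a calibrated examiner. The screen has no described comparator, and its readers belong to the group that delivers the intervention.

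This reaches further than one sentence. The model is to estimate the effect of fluoride on the next oral health assessment (lag 1) and on the one after that (lag 2). The AHW screen is the only clinical assessment described between baseline and 30 months. Statistical analysis says the design will give a fluoride estimate free of bias, and the Discussion presents the model as a test of the program's efficacy. If interim screens carry those paths, a lagged coefficient could be reported as evidence of effect when it partly reflects how the workers read and record.

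**Working it through.** The plan attaches no figure to the screen, so there is none to reproduce. Its sample size of 150 concerns the 30-month caries score and does not bear on this point. The check is first a comparison of the two measures.

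| Feature | AHW screen | 30-month examination |
|---|---|---|
| Role in the program | Component of the intervention | Outcome assessment only |
| Reader | AHWs, who also deliver the program | Calibrated examiner |
| Scale | Positive/negative, for early signs | Decayed, missing and filled primary teeth (Study design) |
| Counterpart in reference children | None described | Same diagnostic criteria |
| Place in the endpoint list | Only as the trigger for early referral | Primary endpoint |

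The reference children are already 30 months old in the first year of the program (Methods/Design, primary endpoint). The program could not have screened them at the earlier visit ages. That no screen exists for them is inferred from this; the protocol does not say it outright.

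The trial is single arm, so every family is offered the program. A path from fluoride to the next assessment therefore compares families by recorded use, not by assignment. AHWs record the use and also read the screen. An error that links the two records produces an association by itself.

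**Hypothetical illustration.** All accuracy and prevalence values are assumed; none comes from the protocol. Let p be the true screen-detectable prevalence, the same in recorded toothpaste users and in others, so that there is no true association.

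Share positive = p × Se + (1 − p) × (1 − Sp), with Sp = 0.90 in both groups, Se = 0.80 in others and Se = 0.60 in recorded users.

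- p = 0.30: others 0.24 + 0.07 = 0.31; users 0.18 + 0.07 = 0.25; relative risk 0.25/0.31 = 0.81.
- p = 0.40: others 0.32 + 0.06 = 0.38; users 0.24 + 0.06 = 0.30; relative risk 0.30/0.38 = 0.79.
- p = 0.50: others 0.40 + 0.05 = 0.45; users 0.30 + 0.05 = 0.35; relative risk 0.35/0.45 = 0.78.

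With Se = 0.70 in users, the relative risks are 0.28/0.31 = 0.90, 0.34/0.38 = 0.89 and 0.40/0.45 = 0.89. With equal sensitivity the relative risk is 1.

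The error can also run the other way. At p = 0.40 and Se = 0.80 in both groups, Sp = 0.90 in users and 0.95 in others gives 0.38 against 0.32 + 0.03 = 0.35, a relative risk of 1.09. Neither the sign nor the size of any bias can be known from the protocol.

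**The case against.** The strongest reply is that nothing important depends on the screen. The primary endpoint, the primary analysis and the case for Phase III all use the 30-month examination. The screen result is not a listed endpoint. It enters the list only through early referral, which is to be analysed descriptively. The sentence at issue closes the modelling text, where it most naturally names the model's interim and final outcomes, and the protocol calls that model one potential model. All of this stands, and it limits the point to a secondary use. A reader might infer from the sentence that the screen ranks equally with the examination throughout the trial, or that the main result is compromised. The rest of the protocol does not support either reading.

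A second reply is that measurement error is addressed: the screen has a cited source, and reliability estimates for single-indicator variables are promised from pilot work and published evidence. This stands against calling the screen unverified. It does not answer the point, because reliability deals with random error. It neither corrects error related to delivering the program nor supplies a comparator.

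A third reply is that lagged paths within the cohort do not need screens in reference children. That is correct for estimating an association. It is not enough for a claim of program efficacy.

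Two further inferences go beyond the text. One is that the individual who taught a family also reads its screen. The protocol shows only that AHWs as a group do both, with up to three per service. The other is that screen rates will be compared with the 43% in the Background or judged against the planned 20% reduction. No such comparison is planned: the 43% comes from Northern Territory examinations, and the 20% is a fall in a mean score from 2 to 1.6.

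**Conclusion.** The point holds as a limit on what screen-based results can show. The protocol names the screen as a measure of effectiveness, yet it is part of the program, is read by the deliverers' group and has no described counterpart in the reference children. Screen results, and the lag-1 and lag-2 paths so far as they use interim screens, cannot by themselves show program effectiveness. They do not support the language of unbiased estimation or of testing efficacy.

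The primary conclusion is not touched. The size of any bias is unknown; the relative risks above show only that modest differences in reading could create an association where none exists. The conclusion assumes that the reference children have no comparable screens and that the model's interim oral health variable draws on the AHW screen. Figure 3 is not available to confirm the second assumption.

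**What to change.** 1. In the sentence after Figure 3, state that effectiveness is judged on the calibrated 30-month examination only.
2. Describe the screen as a program component and the trigger for the early-referral endpoint. Label screen-based results and model paths as exploratory within-cohort associations, and bring the bias-free estimation claim in Statistical analysis and the efficacy claim in the Discussion into line.
3. Where an AHW screen is recorded at or near the 30-month visit, record it before the examiner's result is known. Cross-tabulate the two, and report sensitivity and specificity with 95% confidence intervals as a feasibility result. Say which examiner finding counts as positive, because the screen looks for early signs.

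The table would be informative but rough. With 150 × 0.67 ≈ 100 children examined and an assumed prevalence of 0.40, a sensitivity of 0.80 rests on about 40 children and has a half-width of 1.96 × √(0.80 × 0.20/40) = 0.12 (0.14 at prevalence 0.30, 0.11 at 0.50). A specificity of 0.90 on about 60 children has a half-width of 1.96 × √(0.90 × 0.10/60) = 0.08. This ignores clustering by worker.

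The cost is a few sentences, one table and a rule on the order of recording. The visit schedule is in Figure 1, which is not available. If no screen falls near 30 months, step 3 would need an added one and can be left out; steps 1 and 2 are the essential correction. The downside is that interim screens no longer count as evidence of effect.
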